## Abstract

**Background:**

Tobacco consumption during pregnancy is one of the most modifiable causes of morbidity and mortality for both pregnant smokers and their foetus. Even though pregnant smokers are conscious about the negative effects of tobacco consumption, they also had barriers for smoking cessation and most of them continue smoking, being a major public health problem. The aim of this study is to determine the effectiveness of an application (App) for mobile devices, designed with a gamification strategy, in order to help pregnant smokers to quit smoking during pregnancy and in the long term.

**Methods:**

This study is a multicentre randomized community intervention trial. It will recruit pregnant smokers (200 participants/group), aged more than 18 years, with sporadically or daily smoking habit in the last 30 days and who follow-up their pregnancy in the Sexual and Reproductive Health Care Services of the Camp de Tarragona and Central Catalonia Primary Care Departments. All the participants will have the usual clinical practice intervention for smoking cessation, whereas the intervention group will also have access to the App. The outcome measure will be prolonged abstinence at 12 months after the intervention, as confirmed by expired-carbon monoxide and urinary cotinine tests. Results will be analysed based on intention to treat. Prolonged abstinence rates will be compared, and the determining factors will be evaluated using multivariate statistical analysis.

**Discussion:**

The results of this study will offer evidence about the effectiveness of an intervention using a mobile App in smoking cessation for pregnant smokers, to decrease comorbidity associated with long-term smoking. If this technology is proven effective, it could be readily incorporated into primary care intervention for all pregnant smokers.

**Trial registration:**

Clinicaltrials.gov ID NCT05222958. Trial registered 3 February 2022.

**Supplementary Information:**

The online version contains supplementary material available at 10.1186/s12884-022-05250-5.

## Background

Tobacco consumption during pregnancy is the leading preventable cause of morbidity and mortality for both pregnant and the future child. Smoking in pregnancy has detrimental perinatal effects, including placental abruption, congenital malformations, preterm birth, low birth weight and even miscarriage. Moreover, after gestation, it is associated with cardiac and respiratory problems, hyperactivity, obesity and decreased academic performance in the child [1, 2]. Even though, it has been estimated that 12-22% of pregnant women in industrialized countries smoke during pregnancy [3]. In Spain, 28.3% of women in reproductive age smoke daily and between 30–40% of pregnant women are active smokers at the beginning of pregnancy [4, 5]. Although, around 40% of them quit smoking before or during pregnancy, more than 40 or 85% relapse at 6 or 12 months postpartum, respectively [6].

Pregnancy is considered an ideal opportunity to intervene and control tobacco consumption among smokers and their families [4, 7]. However, the lack of knowledge and education about the harmful effects of smoking during pregnancy is related to higher smoking prevalence, having a further impact in people with either lower socio-economic status or educational level [8, 9]. Different preventive strategies for tobacco consumption are carried out by primary care, such as behavioural support or pharmacotherapy [7]. Although these interventions reduce tobacco consumption in the general population, pregnant smokers do not use to request for them [4, 10, 11]. Actually, potential barriers that make smoking cessation difficult in this population include the social stigma and fear of being judged, as well as the negative attitudes towards the support provided by health care. These facts lead to underestimated rates of smoking prevalence [12, 13]. Thus, the development of alternative strategies on smoking cessation support, specifically adapted to pregnant smokers, is needed.

The generalised use of smartphones and the increasing omnipresence of the internet in these devices, prompted the development of health promotion Apps. Spain is one of the European countries’ leaders in the use of smartphones and health-related topics are among the most searched information. In Spain, it is estimated that around 5 million people use Apps, and their average profile corresponds to young people of reproductive age, between 25 and 40 years old [14]. However, the evaluation of efficacy of health-related Apps is still limited [15]. Recent systematic meta-analysis reported that digital interventions containing behaviour change techniques focused on goals and planning could be effective for smoking cessation during pregnancy [16]. In accordance, interventions that include behaviour change through "problem solving", "information about health consequences", "information about social and environmental consequences", "social support", "negative emotions reduction" and "instructions on how to make behaviour change" are more successful in smoking cessation even after delivery [17]. Recently, many Apps have been developed for pregnant smoking cessation in different countries, including the “SmokeFree Baby” App in the UK that was satisfactory valuated by participants [18].

Previous studies from our research team, determined the effectiveness of an intervention based on gamification and implementation of the Tobbstop App for reducing the prevalence of tobacco use in young population [19]. Beside reducing prevalence of tobacco consumption, 57.7% of habitual users from the Tobbstop App were still abstinent at 12 months [20]. Considering the success of this App, it was implemented in a pilot study of a randomised controlled trial in pregnant smokers [21]. This study revealed a higher percentage of pregnant users from the App that continued their abstinence until delivery in comparison to the control group [21]. Nevertheless, further research is needed in this area with larger samples and longer follow-up periods to replicate the findings of this study and to ensure continued abstinence in the postpartum.

Thus, in the present study, we pretend to adapt the Tobbstop App as an intervention for smoking cessation in pregnant smokers and in the long term. The adaptation of the App will be based on educational content, support for smokers, leisure, games, entertainment, and use of the social network itself, based on the clinical practice guidelines for smoker support of the Catalan Institute of Health and the Department of Health [7, 22].

## Methods

### Study objectives

The primary objective of this research is to evaluate the effectiveness of an intervention against tobacco in pregnant smokers based on the Tobbstop App, which has already been validated for smoking cessation in the general population [19, 20].

The specific objectives which have set out are:To determine the effectiveness of the intervention on smoking cessation during pregnancy.To evaluate the effectiveness of the intervention on prolonged abstinence.To analyse the impact of the intervention to reduce daily consumption in pregnant smokers who continue smoking.To determine the impact of the intervention on pregnancy, birth and neonatal health indicators.

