**Smoking habit follow-up**		
Current consumption	Cigarettes/day	Follow-up
Relapse	Yes; No	Follow-up
Date of Relapse	dd-mm-yyyy	Follow-up
eCO test	<10 ppm, smoking abstinence; >10 ppm, active smoking	Follow-up/End
Cotinine test in urine	<100 ng/ml, smoking abstinence; 100 - 500 ng/ml, occasional smoker; > 500 ng/ml smoker	End

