### Follow-up and data collection

During the pregnancy period, follow-up of the study will be adapted according to the pregnancy calendar in the ASSIR. If participants did not attend the follow-up visit in the ASSIR, they will be called by phone to ensure participant’s continuance with the study and to evaluate smoking habit (see Fig. 2). If telephone interviews coincide with a pregnancy visit in the ASSIR, the telephone call will be avoided. After the birth, telephone interviews will be planned monthly to evaluate smoking habits in the long term.

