**Fig. 2 Fig2:**
[figure not shown]
Chronogram of planned follow-up visits during the study and according to the usual follow-up pregnancy visits. LMP, last menstrual period; EDD, estimated date of delivery; gw, gestational week; ppw, postpartum weeks; w,week; m,month. † In case that usual follow-up visits were not possible, telephone interview will be conducted

Smoking habits will be assessed by questionnaire in the scheduled pregnancy follow-up visits and by telephone interviews. Exhaled carbon monoxide (eCO) will be measured, by an eCO monitor, in every scheduled pregnancy visit.

12 months after the basal visit (when participants receive counsel to quit smoking), smoking habit will be evaluated and those participants reporting smoking abstinence, eCO and urinary cotinine tests will be performed.

Lost to follow-up will be considered [1] when the participant decide to quit the study, [2] when the participant do not attend one of the visits and is impossible to contact with them by telephone call and, [3] when pregnancy follow-up is derived to another healthcare unit (high risk obstetric) or another centre.

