### Blinding

Given the nature of the intervention, it is not possible to mask the participants neither the ASSIR professionals to the study group assignments. The data will be masked for the research team carrying out the statistical analyses.

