## Discussion

The purpose of this study is twofold. Firstly, we aim to test the effectiveness of the Tobbstop App for smoking cessation in pregnant smokers. Secondly, we want to assess the impact of the intervention in pregnancy, birth and neonatal health indicators. Mobile health interventions provide solutions for patient empowerment and facilitate effective behavioural changes in different health areas, including smoking cessation [26].

Tobbstop App has been designed to encourage the general population during the process of smoking withdrawal. Recent results showed its efficacy in smoking cessation in young population [20]. Moreover, a pilot study reported a slightly significant result in increasing smoking abstinence in pregnant smokers [21]. According to these, some Apps with digital smoking cessation interventions designed specifically for pregnant smokers have demonstrated promising results [26]. Particularly, pregnant smokers and women of reproductive age are frequent users of the internet, social media, and mobile Apps, being a prime candidate population for mHealth-supported health care.

Nowadays, there is still a stigma surrounding unhealthy habits during pregnancy, joint to the social belief that pregnancy and motherhood should be a state of happiness. These factors, make more difficult for pregnant smokers searching for help and support to quit smoking, and even they used to lie about their tobacco consumption behaviour [27]. In accordance, offering this intervention through a smartphone App will allow its use without time and place restriction. Thus, ensuring a private and anonymous situation inside the App become an advantage in comparison to other social interventions.

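### Objective 3 (reduced consumption) rests on self-reported cigarettes/day in an unmasked trial, and the article contradicts itself on whether women who still smoke have exhaled CO measured at all

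*Protocol article*

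**What the plan says.** Study objectives, third specific objective: "To analyse the impact of the intervention to reduce daily consumption in pregnant smokers who continue smoking".

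The follow-up block of Table 2 gives current consumption as "Cigarettes/day". Follow-up and data collection says how it is obtained: "Smoking habits will be assessed by questionnaire in the scheduled pregnancy follow-up visits and by telephone interviews". For the period after delivery: "After the birth, telephone interviews will be planned monthly to evaluate smoking habits in the long term".

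On masking, the Blinding section says that "it is not possible to mask the participants neither the ASSIR professionals to the study group assignments"; only the analysts are masked. The Discussion says of pregnant smokers that they find it harder to seek help "and even they used to lie about their tobacco consumption behaviour".

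On eCO there are two statements. Follow-up and data collection says that it "will be measured, by an eCO monitor, in every scheduled pregnancy visit", without restricting this to women who report having stopped. Table 1 marks eCO at the usual pregnancy visits and the last visit, and its footnote limits eCO and cotinine to verifying abstinence that the woman has reported. Table 2 lists eCO as "<10 ppm, smoking abstinence; >10 ppm, active smoking". Outcomes assessment and Statistical analysis name abstinence outcomes only, and neither gives eCO a part in judging reduction.

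**The concern.** Abstinence at 12 months has a biochemical check; consumption has none. The women know whether they have the App, and so do the midwives who ask them how much they smoke. If App users shade their answers more than controls do, the App appears to reduce smoking when it does not. The reading that could help to tell the two apart is already in the schedule under one passage and excluded under another.

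A later analysis plan could not repair this. Whether a continuing smoker blows into the monitor, and whether the number is kept, is settled at the visit. If sites follow the Table 1 footnote, no objective reading will exist for the very women whom Objective 3 concerns.

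**Working it through.** **Passages side by side**

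| Question | Follow-up and data collection | Table 1 footnote |
|---|---|---|
| Who has eCO at a pregnancy visit? | No restriction stated | Only women reporting abstinence |
| Reading for a continuing smoker? | Yes, in both arms, during pregnancy | None |

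After delivery the two agree in effect: the monthly contacts are by telephone, and the 12-month tests are confined to women reporting abstinence. Any reduction after birth therefore rests on self-report under either reading. The App's own daily smoking log (Data recording and storage) cannot fill the gap, because controls have no counterpart.

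**Illustration of size**

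The article gives no effect size, SD or power for Objective 3, so there is no figure of its own to reproduce.

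Inputs:
- 200 women per group and control abstinence of 0.50 (Sample size/power calculation).
- Assumption: the App has no effect, so 0.50 applies to both arms and 200 × (1 − 0.50) = 100 continuing smokers per arm. The article does not state 0.50 for the pregnancy period, so this count is itself approximate.
- Assumption: extra under-reporting d in the App arm of 0, 0.5 or 1 cigarette/day.
- Assumption: SD of reported cigarettes/day of 4, 5 or 6.

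Formula: z = d / (SD × √(1/100 + 1/100)), with √0.02 = 0.1414. Chance of p<0.05 = Φ(z − 1.96) + Φ(−z − 1.96).

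For d = 1:
- SD 4: z = 1/(4 × 0.1414) = 1.768; chance 42%.
- SD 5: z = 1/(5 × 0.1414) = 1.414; chance 29%.
- SD 6: z = 1/(6 × 0.1414) = 1.179; chance 22%.

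For d = 0.5, z halves to 0.884, 0.707 and 0.589, and the chance is 14%, 11% and 9%.

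For d = 0, that is, under-reporting that is equal in both arms, the chance is 5% whatever the SD.

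Taking off the planned 5% loss (95 v 95) changes little: for d = 1 the chances are 41%, 28% and 21%.

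**The case against.** **Misreporting in general is not misreporting by arm.** The Discussion's remark covers all pregnant smokers. Equal under-reporting leaves the false-positive rate at 5%, as the last case above shows. Nothing in the article documents a difference between arms. Daily logging in the App might sharpen recall and raise reported counts, and App access ends 90 days after D-day while follow-up runs to 12 months. This stands. A reader might infer that a reduction in the App arm would be nothing but under-reporting; the article supports only that this could not be excluded.

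**Table 2 does not prove that the ppm value is thrown away.** A reader might take the split at 10 ppm as showing that only a class is stored. But Table 2 also lists bands for the Fagerström, Richmond and Apgar scores and for cotinine, all of which have a numeric value, and the collection form (Supplementary data 1) is not shown. This stands too. The request is to make sure that the number is kept.

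**The choice of variable and model for a secondary objective may be in a fuller document.** That is fair for the model. It does not remove the contradiction over who is measured, which is in the text shown.

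**A larger figure would be easy to produce and wrong.** Comparing all 200 v 200 women with a full 1-cigarette shift would apply under-reporting to abstainers, who have nothing to under-report. Using 100 v 70 smokers (from 0.50 and 0.65) would assume that the App works while calling it ineffective. Neither belongs here.

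**Conclusion.** The point holds as a limit on what Objective 3 can show, together with a contradiction in the text that has to be resolved. As the article stands, reduction is judged on self-report in an open trial, and whether an objective reading exists for continuing smokers depends on which passage a site follows. The gap is firmest after delivery, where no objective reading is planned for them under either passage.

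The 22% to 42% range illustrates how a modest reporting difference could pass as an effect. It rests on an assumed 1 cigarette/day differential, an assumed SD of 4 to 6 and about 100 smokers per arm. At half that differential it is 9% to 14%, and at none it is 5%. It is not an estimate of what will happen. Objective 3 is a secondary aim, and the primary outcome, prolonged abstinence at 12 months with eCO and cotinine confirmation, is not called into question by this point.

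**What to change.** 1. Reconcile the Table 1 footnote with Follow-up and data collection so that eCO is measured in every participant at each scheduled pregnancy visit, whatever she reports. Cotinine can stay limited to reported abstainers.
2. Make sure that the ppm value is stored as well as the class at 10 ppm.
3. Report eCO by arm as a supportive objective measure beside cigarettes/day: for example, log ppm at the last pregnancy visit in all randomised women, adjusted for basal cigarettes/day (Table 1 marks no basal eCO).
4. Label Objective 3 as self-reported and exploratory wherever no eCO exists, including the telephone follow-up after birth, and claim no reduction from self-report alone.

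Agreement in direction should not be treated as proof. With no true effect, and eCO independent of reporting bias, the sign of the eCO difference is about a coin toss, so requiring agreement would only about halve the false-positive rate (29% × 0.5 ≈ 15% at SD 5). The size and interval of the eCO difference should be shown.

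The cost is small: the monitor and visits are already planned, so the change is an aligned footnote, a numeric field to check and one further model. There are two drawbacks. By the article's own account eCO reflects only the previous 12 to 24 hours, so it is noisy. And a model in all women mixes quitting with reduction, although it avoids comparing a subgroup formed after randomisation.

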### Study design

This study consists on a randomised community controlled clinical trial to evaluate the effectiveness of the intervention on smoking cessation.

The general framework of this study is shown in Fig. 1 and the activities to be carried out at each visit are detailed in Table 1.

**Fig. 1 Fig1:**
[figure not shown]
Flowchart of the TOBBGEST study: process of selection, randomization, and follow-up visits

**Table 1 Tab1:** Diagram of activities to be carried out by participants at each visit

	**Basal visit**	**Usual calendar pregnancy visits**	**Telephone visits**	**Last visit**
**Procedures:**				
Planning day D	X			
Smoking habit	X			
Sociodemographic variables	X			
Clinical history of comorbidities and risk factors associated with tobacco use	X			
Basic physical examination	X	X		
Lifestyles and habits	X	X		
Pregnancy variables	X			
Biochemical measures during pregnancy follow-up		X		
Smoking habit follow-up*		X	X	X
Birth indicators		X		
Newborn health indicators		X		
**Intervention:**				
Control group: 5A’s strategy	X	X	X	X
Intervention group: 5A’s strategy + access to App Tobbstop	X	X	X	X
**Confirmation of smoking abstinence:**				
eCO test		X^*$*^		X^*$*^
Cotinine test in urine				X^*$*^

If the telephone visit and the face-to-face visit coincide, the telephone visit will be omitted

*Relapse. In case of relapse, the following data should be collected: the presence of withdrawal symptoms, if she is still taking the prescribed treatment and if she has smoked a puff

^*$*^eCO and cotinine tests will be taken only to confirm the smoking abstinence reported by the participant

### Study setting

The Sexual and Reproductive Health Care Services (in Catalan, *Atenció a la salut sexual i reproductiva*—ASSIR) is a public Catalan Healthcare service of assistance and educational activities related to orientation and family planning, specific and confidential attention to young people, control and monitoring of pregnancy, among others.

This study will be conducted at the in the ASSIR from the primary care centres of the Camp de Tarragona and Central Catalonia regions (Spain), which are composed of midwives, gynaecologists-obstetricians, nurses, psychologists and administrative personal.

Specifically, pregnancy monitoring centres participating in the recruitment of the study will be four, all of them from the Catalan Institute of Health: three in the Tarragona region (Tarragona, Reus and Valls) and one in the Central Catalonia region (Vic).

All midwives and gynaecologist from the participating centres are invited to collaborate in the study as associate researchers. They will received standardized formation about the methodology of study and the use of App.

### Participant selection

Pregnant smokers visiting the ASSIR centres for any medical reason will be invited to participate if they meet all the inclusion, but none exclusion criteria’s (selection visit).

#### Inclusion criteria

Pregnant smoker (< 28 gw) aged more than 18 years old.Follow-up of pregnancy in the ASSIR units selected.Active smokers, who report having smoked sporadically or daily in the last 30 days, at least one cigarette.Having a mobile device with Android or iOS operating system and data connection.Having skills on the use of Apps and willingness to use them (*).

#### Exclusion criteria

Consonant smokers or in the Pre-contemplation stage, according to Prochaska and DiClemente’s model [23].Having participated in a smoking cessation study within the last 12 months.Psychiatric history that prevents or limits follow-up of the study.Having another substance dependence or abuse, apart from tobacco consumption.Currently under a smoking cessation treatment.Impossibility of follow-up participation for any reason.Patient refusal to participate or withdrawal from the study.

(*) It is understood that you have skills on the use of Apps and willingness to use them if you answer affirmatively to the following questions:i.Have you downloaded any application on your mobile?ii.Would you install an application to help you quit smoking on your mobile?iii.Have you participated in any chat group?iv.Have you played any game with your mobile device? (Criteria to ensure the usability of the intervention tool).

### Recruitment, data collection and randomization

#### Recruitment (selection visit)

Participants will be recruited through referrals of midwives from the participating centres. During the selection visit, all pregnant smokers will be advised that smoking during pregnancy could cause detrimental effects for themselves and their foetuses and smoking cessation will be recommended. All eligible participants, will be informed about study characteristics and offered the possibility of participating. If pregnant smoker are interested in taking part of the study, a booklet with additional details will be delivered.

Those eligible participants who agree will be asked to provide signed informed consent and a basal visit will be planned (according to their pregnancy visits) to provide counselling on smoking cessation and the indications to start with the study.

The study is conducted in agreement with the principles of the Helsinki Declaration and the guidelines of Good Clinical Practice. All participants give written informed consent prior to the study enrolment. The protocol has been submitted to the Clinical Research Ethics Committee (CEIC) of the Primary Care Research Institute (IDIAP) Jordi Gol (21/297-P; 15/12/2021) and pending to be approved.

